*PAXgene tube*. Once collected, samples need to remain at room temperature for 2 hours. After this, samples may be stored in a -80 C freezer and then batch shipped to the University of Utah on dry ice.

*Yellow top #2*. Samples should be centrifuged for 10 minutes at 4000 RPM at 4 C immediately after collection. The supernatant (plasma) should be aspirated, divided into 3 aliquots, and stored in new tubes. The samples should be placed at -80 C immediately, then batch shipped to the University of Utah on dry ice.

*Urine sample.* The urine sample will be divided in two 5 ml tubes and stored at -80 C for batch shipping.

*Electrocardiogram (ECG).* This will be performed at each visit to evaluate the extent of cardiac conduction disease. PR interval and QRS duration will be determined using standard methods.

*Muscle biopsy sub-study*. The biopsy sub-study will examine RNA splicing defects that are characteristic of DM1. The proposed study builds on results from the initial DMCRN study, in which we obtained paired needle biopsy samples of tibialis anterior muscle from 97 patients. The samples were obtained 3 months apart to approximate the expected time course of muscle sampling in early-phase clinical trials. No significant safety issues were encountered. The biopsy procedure was well tolerated and > 95% of subjects who underwent the initial biopsy returned for the second biopsy. The second biopsy was obtained from the same leg, except in 19 patients whose second biopsy was obtained from the opposite leg. RNAseq of biopsy samples has now been completed and the preliminary analyses indicate that test-retest reliability of splicing biomarkers was substantially better for paired samples obtained from opposite legs. We seek now to confirm this finding in an independent cohort. Furthermore, in discussions with FDA officials about splicing biomarkers, the question was raised whether RNA splicing defects observed in tibialis anterior are representative of other muscles. Therefore, we are also testing whether splicing misregulation in an arm muscle, biceps brachii, is similar to that in tibialis anterior.

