*Needle biopsy procedure.* 60 participants will undergo a muscle biopsy at the baseline visit and again at a three month study visit. The biopsy procedure is the same as our previous studies. After skin preparation using povidone-iodine or equivalent antiseptic, the skin and subcutaneous tissues will be anesthetized with 7-10 ml of 0.5% or 1% lidocaine, without epinephrine. The biopsy will be performed using side-cut biopsy needles, core biopsy needles, or the newer Vacora vacuum-assisted biopsy system. For side-cut needles (known as Bergstrom or UCHL needles) or Vacora 14 g biopsy probes, a 3‑mm incision will be made in the skin and muscle fascia, and muscle tissue will be obtained with 1 to 3 passes of the biopsy needle. Closure of the incision is obtained with steristrips or topical skin adhesive. For core biopsy needles (14 gauge, 10 mm length) a skin incision is not required, and 2 to 4 passes of the biopsy needle will be performed. Biopsy specimens (5 to 40 mg) will be frozen in liquid nitrogen within 2 minutes of removal, stored at -70C, and shipped in batches to the University of Rochester for targeted high-throughput RNA sequencing. A repeat biopsy will be obtained three months later from the opposite tibialis anterior (*n* = 40) or biceps (either side, *n* = 20). The site investigator will determine which site is used for the second biopsy, based on degree of muscle weakness and muscle atrophy. To enable comparisons across muscles having similar weakness, half of the biceps biopsies will be obtained from subjects having at least slight weakness of elbow flexors (MRC score ≤ 4+). Ultrasound may be used to guide needle biopsies of biceps, generally this is not necessary for tibialis anterior.

- 1. Genetic test for CTG expansion at the DM1 locus

Genomic DNA extracted at baseline will be analyzed by PCR, Southern blot, or both, to determine length of the CTG repeat as previously described.4 Repeat length may also be determined using higher resolution procedures as they become available. Repeat-primed PCR will be used to test for variant repeats (CCG or CGG repeats embedded within the CTG repeat tract) as previously described.5 DNA samples from the 12 and 24 month study visits may be used to assess test-retest reliability of repeat length measurements.

- 1. Genotyping procedure for GWAS

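### The biopsy sub-study sets out to confirm that opposite-leg pairs are more reliable than same-leg pairs, but it collects no same-leg pair and can only estimate opposite-leg reliability

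*Protocol*

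**What the plan says.** Protocol section 5, under the heading on biomarkers and the muscle biopsy substudy, gives the rationale. In the initial network study, "we obtained paired needle biopsy samples of tibialis anterior muscle from 97 patients". Of these, "The second biopsy was obtained from the same leg, except in 19 patients whose second biopsy was obtained from the opposite leg". Preliminary analyses indicated that "test-retest reliability of splicing biomarkers was substantially better for paired samples obtained from opposite legs". The aim follows directly: "We seek now to confirm this finding in an independent cohort".

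The paragraph on the needle biopsy procedure fixes what is collected: "60 participants will undergo a muscle biopsy at the baseline visit and again at a three month study visit". For the second sample, "A repeat biopsy will be obtained three months later from the opposite tibialis anterior (*n* = 40) or biceps (either side, *n* = 20"). The choice between the two muscles is not randomised: "The site investigator will determine which site is used for the second biopsy, based on degree of muscle weakness and muscle atrophy".

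The protocol states no comparison with the same-leg pairs of the initial study.

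**The concern.** The result to be confirmed is comparative. One kind of pair was more reliable than the other, so confirming it in an independent cohort needs both kinds of pair in that cohort. As designed, the new cohort supplies one kind.

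Optimising sample collection and analysis for splicing biomarkers is one of the three purposes in section 1. The three-month interval was chosen to resemble muscle sampling in early-phase trials. If the 40 new pairs show good reliability, the present wording invites the conclusion that biopsy side is the reason. The data could not separate side from anything else that changed between the two studies.

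**Working it through.** **Counting the pairs**

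| | Same-leg TA | Opposite-leg TA | TA then biceps | Total |
|---|---|---|---|---|
| Initial study | 97 − 19 = 78 | 19 | – | 97 |
| This sub-study | 60 − 40 − 20 = 0 | 40 | 20 | 60 |

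The stated total reproduces: 40 + 20 = 60. Each participant has two biopsies, so no same-leg pair can arise elsewhere. The biceps pairs are no substitute, because they change the muscle. With no same-leg pair, the difference between opposite-leg and same-leg reliability cannot be estimated within the new cohort, however many participants are enrolled.

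**What the 40 pairs can estimate**

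The protocol gives no reliability figure and no precision calculation for the sub-study, so the ICCs below are assumptions. On the Fisher z scale the 95% interval is tanh(atanh(ICC) ± 1.96 × SE), with SE = 1/√(n − 1.5). For n = 40, SE = 1/√38.5 = 0.161.

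| Assumed ICC | atanh | 95% interval, 40 pairs |
|---|---|---|
| 0.70 | 0.867 | 0.50 to 0.83 |
| 0.80 | 1.099 | 0.65 to 0.89 |
| 0.90 | 1.472 | 0.82 to 0.95 |

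This is a useful single-group estimate. It is not a comparison.

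**What an external comparison would rest on**

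The only same-leg pairs are the 78 from the initial study. Three points limit them:

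- They are one side of the contrast that produced the finding, so that side of the comparison is not independent.
- The initial samples had RNAseq, whereas the new samples are to have targeted high-throughput RNA sequencing. The Background also says that this study will refine sample collection and analysis in order to improve reliability. Either change could alter within-pair variation without any effect of side.
- The site investigator chooses TA or biceps by weakness and atrophy, so the 40 TA pairs are a selected group.

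**Why within-pair SD and not the ICC**

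ICC = B/(B + W), where B is the between-patient and W the within-pair variance. As an illustration, assume W = 0.25 throughout. A between-patient SD of 1.0 gives 1/(1 + 0.25) = 0.80, and an SD of 0.7 gives 0.49/(0.49 + 0.25) = 0.66. Measurement error is the same in both, so across two cohorts the ICC mixes patient spread with reliability. The example shows only that the scale matters. A narrower spread would make the new pairs look worse, so it does not demonstrate a bias towards false confirmation.

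**Power for a comparison of within-pair variances**

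Two-sided F test at 0.05, with one degree of freedom per pair (no systematic shift between visits) and assumed variance ratios:

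| Ratio, same-leg to opposite-leg | Randomised 20 v 20 | 78 earlier v 40 new |
|---|---|---|
| 2 | 32% | 68% |
| 3 | 67% | 98% |
| 4 | 86% | not needed |

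The non-concurrent comparison has more power but carries the three limits above. The 20:20 split removes them but exceeds 80% only at a four-fold ratio.

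**The case against.** Confirming can be read more loosely. The earlier result was preliminary and rested on 19 opposite-leg pairs, and asking whether good reliability recurs in 40 new pairs is a recognisable replication. The sub-study is said to build on the initial study, so the 78 earlier same-leg pairs are a natural benchmark, and how to use them could sit in a statistical analysis plan that is not shown. Section 1 asks only for optimised procedures and states no same-versus-opposite hypothesis. Section 5 also says that the biopsy procedure is unchanged.

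Much of this stands. It limits the point to the confirmation claim and leaves the value of the sub-study intact. It does not rescue the claim: recurrence of good opposite-leg reliability is an estimate for one group, and an analysis plan cannot supply same-leg pairs that the protocol does not collect.

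A reader might infer more than the documents support:

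- **That eligibility is known to differ from the initial study**, through the CTG repeat rule or the weakness quota. The initial study's criteria are not given. The needle biopsy paragraph ties the quota to the biceps biopsies. The sub-study inclusion criteria instead refer to 60 patients having biceps biopsy, which conflicts with 20 and needs reconciling, but neither reading creates a same-leg pair.
- **That a false confirmation will be reported and will set sampling rules for later trials.** The protocol says neither.
- **That same-leg biopsies must be randomised.** The sub-study excludes previous TA biopsy in order to sample unbiopsied muscle, and a same-leg repeat would go back into a biopsied one. With the power shown above, randomisation is a trade-off and not a requirement.

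**Conclusion.** The stated aim and the design do not match. The aim is to confirm a contrast, and the new cohort contains 0 same-leg pairs among 60. This conclusion needs no assumption beyond the protocol's own counts. The sub-study can deliver an opposite-leg reliability estimate, with a 95% interval of about 0.65 to 0.89 if the ICC is 0.80. It can also support a caveated comparison with the 78 earlier pairs. It cannot establish that biopsy side is the cause of better reliability. The intervals and powers rest on assumed ICCs and variance ratios, because the protocol gives none.

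This should be fixed. It changes what the sub-study may conclude, but it does not affect the main cohort's endpoints or make the biopsy data unusable.

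**What to change.** 1. In the muscle biopsy sub-study paragraph of section 5, replace the aim of confirming the initial study's result with the aim of estimating opposite-leg test-retest reliability.
2. Prespecify a comparison of the 40 new opposite-leg pairs with the 78 earlier same-leg pairs. Use within-pair SD and not the ICC, with a common sequencing and analysis pipeline where existing data allow.
3. Label that comparison non-concurrent and non-randomised, and state that it will not be taken as confirming biopsy side as the cause.

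The cost is wording plus re-analysis of existing data, with no additional biopsy.

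If the sponsor wants a within-cohort contrast, it could weigh randomising the 40 repeat TA biopsies between same and opposite leg. That also adds no biopsy, but it has the power shown above, re-samples a biopsied muscle in half of those participants, and widens the opposite-leg interval. With 20 pairs SE = 1/√18.5 = 0.232, so the interval at an ICC of 0.80 becomes 0.57 to 0.91.

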For this study, an *adverse event* is any new, undesirable medical occurrence or change of an existing condition in a subject that occurs during a study visit. An adverse event could be a fall during a 6 minute walk test, a complication during a needle muscle biopsy, etc. We will not capture changes that are occurring as part of the disease progression as an adverse event. These changes will be captured under the Medical History CRF (06) and updated at each visit.

For this study, a *medical event* is any change in symptom, change in frequency, new diagnosis, sickness, hospitalization, surgeries, etc. that happen within the 12 month period that the patient is enrolled in the study. These items will be documented on the Medical History Form (06).

- 1. **Adverse Event and Medical Event Reporting Period**

The recording of adverse events will begin with the start of protocol-specific procedures. Reporting will continue until the last in-person study visit or when a subject ends participation in the study.

- 1. **Reviewing Adverse Events and Medical Events**

Inquiries about medical events will occur at every visit. In addition, subjects will be instructed to contact the study coordinator about any concerns or changes in health status.

Adverse events will be reviewed by with the site investigator and study coordinator at each study visit.

- 1. **Adverse Event and Medical Event Coding**

Coordinators will list a complete description of the adverse/medical event including area of body affected and symptoms. The NMD-CC will code adverse events at the time of data analysis.

- 1. **Adverse Event Follow-up**

The site investigator will review all ongoing adverse events with the subject during each visit and telephone call to evaluate any change in status. All adverse events will be monitored by the treating neurologist until resolution or the end of the study’s AE reporting period. Resolution of an adverse event is defined as a return to the subject’s baseline condition (level of symptoms, laboratory value or frequency of episodes).

The progress of each SAE will be followed by the study PI until resolution or until an appropriate endpoint is reached. An appropriate end point is the resolution of the event or the determination that the event has become chronic or stabilized.

- 1. **Required Reporting Elements**

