Details regarding adverse events will initially be entered in the subject’s progress notes as source documentation. Each adverse event will be recorded on the subject’s Adverse Event Log (CRF 56). All of the required data elements included on the Adverse Event Log must be completed for each event. A description of each item required on the Adverse Event Log is described in sections 2.1a – 2.1h.

8.6.a **Adverse Event Description**

Capture a complete description of the adverse event including the area of the body affected as well as symptoms experienced by the patient.

8.6.b **Record Date**

The date an event is recorded is the day that study staff becomes aware of the adverse event either during a study visit, phone call or through the receipt of test results. A complete date must be entered for this field on the Adverse Event Log.

8.6.c **Severity**

The site investigator or study coordinator will grade the severity of each adverse event using the detailed clinical descriptions provided below. This grade will be entered in the appropriate field on the Adverse Event Log.

The general guidelines for grading each adverse event are based on the following scale:

| **Grade** | **Description** |
| --- | --- |
| 1 | Mild; Asymptomatic or mild symptoms; clinical or diagnostic observations only; intervention not indicated. |
| 2 | Moderate; minimal, local or noninvasive intervention indicated; limiting age-appropriate instrumental ADL |
| 3 | Severe or medically significant but not immediately life-threatening; hospitalization or prolongation of hospitalization indicated; disabling; limiting self care ADL |
| 4 | Life-threatening consequences; urgent intervention indicated. |
| 5 | Death related to AE. |

A semi-colon reads as the word ‘or’ within the description of the adverse event’s grade.

8.6.d **Action Taken**

The actions taken to manage adverse events must be recorded using the terms listed in the table below. A minimum of one term must be entered for each adverse event. Multiple actions can be entered.

- None
- Hospitalization
- Terminated from the study
- Unknown
- Medication
  Other

Any changes in concomitant medication must be recorded on the Concomitant Medication Log (CRF26).

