The term “Hospitalization” refers only to inpatient hospitalization. “Hospitalization” should not be recorded if a subject was admitted as an outpatient for a procedure. Outpatient procedures can be documented as a response to an adverse event using the code “Other.” The subject’s source documentation will capture information about the procedure.

8.6.e **Seriousness**

The site investigator will evaluate if the adverse event meets the criteria for being a Serious Adverse Event. A Serious Adverse Event (SAE) is defined as any adverse event that:

- Results in death
- Is life-threatening or places the participant at immediate risk of death from the event
- Requires inpatient hospitalization or prolongation of existing hospitalization. Hospitalizations scheduled before enrollment for an elective procedure or treatment of a pre-existing condition which has not worsened during participation in the study will not be considered a serious adverse event.
- Causes persistent or significant disability/incapacity (substantial disruption of one's ability to conduct normal life functions) that is not related to the underlying myotonic dystrophy
- Results in a congenital anomaly/birth defect
- Is a medically important event that required medical intervention to avoid one of the above outcomes

If an AE meets the criteria for being serious, the AE must be listed on the primary Adverse Event Log (CRF56) and additional information must be submitted using the Serious Adverse Event Form (CRF57). Additional instructions on reporting Serious Adverse Events are located in section 3.0.

8.6.f **Outcome**

Resolution of an adverse event is defined as a return to the subject’s baseline condition (level of symptoms, laboratory value or frequency of episodes). Otherwise, mark the outcome as “ongoing.”

8.6.g **Start Date**

The start date is the day an adverse event begins

If study personnel are unable to determine an exact date based on the subject’s report or available records, the study personnel must estimate a start date using the information available. Additional details for entering dates are included in the study manual section, Data Collection and Documentation.

8.6.h **End Date**

The end date is the day an adverse event resolves or the subject returns to their baseline condition.

If study personnel are unable to determine an exact date based on the subject’s report or available records, the study personnel must estimate an end date using the information available.

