**8.14 SAE Data Management**

Original copies of all CRFs generated for the SAE must be entered in REDCap.

The information that is reported on Serious Adverse Event Form (CRF57) and SAE Follow up Form (CRF58) must correspond to the information that is entered on the subject’s primary Adverse Event Log (CRF56). The adverse event term, dates and ratings must be consistent between forms. It is the site’s responsibility to ensure that all data is reported accurately. The data manager will review the data that was submitted and will query any fields where there are discrepancies.

If a discrepancy is noted by study personnel, the error will be corrected in the database. If a discrepancy is discovered by the NMD-CC, the site will be sent a Data Clarification Form.

1. **RISK/BENEFIT ASSESSMENT**
   1. **Potential Risks**

The procedures described pose minimal risk. Release of medical information prior to participation could result in a potential loss of privacy.

There is a small risk of bruising from blood draws and muscle soreness from the QMT, MMT, maximum voluntary isometric contraction grip testing, and functional tests.

Risks of the muscle biopsy include bruising, pain, and muscle soreness in the area of the biopsy. There may be a small, permanent scar on the skin from the incision. There will also be the risk of bleeding, infection, and numbness (from touching a nerve with the needle). There is the rare risk that a person might be allergic to lidocaine with reactions that could range from mild skin rash to anaphylactic shock (drop in blood pressure, breathing difficulties).

- 1. **Protection Against Risks**

All patients will be monitored closely by the study site nursing staff and Investigators during the procedures to prevent and/or minimize any potential risks or discomfort. The nursing staff and study personnel will receive in-service training regarding these procedures. Each participant will be asked to report any continuing discomfort caused by any of the procedures.

Patients will be withdrawn from the study if intolerable side effects or serious AEs, as determined by the Investigator, are identified. Patients who cannot tolerate the procedures or who develop other illnesses that affect the evaluations may be withdrawn from the study. Patients may withdraw at any time.

- 1. **Potential Benefits to Subjects**

There are no direct benefits that patients may expect to receive as a result of participation in this study.

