Both anchor-based and distributional methods for determining the minimal clinically important difference (i.e., the minimum degree of change in scores that are deemed significant) will be used. The standard error of the measurement (SEM) will be calculated by multiplying the SD of the baseline measurement by the square root of the difference of 1 minus the ICC of the measure.7 The 90% minimal detectible change is calculated by multiplying the standard error of the measurement by the the square root of 2 by the Z-score for a cut-off of 90% distribution (1.65). A multiple anchor technique will also be utilized to describe the responsiveness of the motion analysis metric as described by Guyatt et al. and elsewhere.8-10 The clinical outcomes will be compared among the categories of “domain delta” (e.g.: unchanged, a little better, a lot better, etc.) using the Jonckheere-Terpstra test. This test, which is designed to detect differences among ordered classes, is more powerful than tests that do not account for the ordering among the classes, such as the Kruskal-Wallis test. This method can also be used to help determine the minimal important difference (MID). The responsiveness to change index will be assessed by dividing the absolute change scores in the DM1 group with stratification at the subgroup level (e.g., age, gender). All statistical significance will be set at alpha of 0.05 at two-tailed. Go-no go decision point for each outcome measure will be set for a responsive index of at least 0.5. This decision will be reviewed by the study investigators and advisory panel periodically during the project period and adjusted as necessary.

- 1. **Data and Safety Monitoring**

Due to the routine risks associated with this protocol and lack of therapeutic interventions, the proposed study will not require a Data Safety and Monitoring Board. The Coordinating Investigators (Drs [name] and [name]) will be responsible for the safety monitoring of the study. Summary data regarding complications from the muscle biopsy procedure and results of post-biopsy follow up calls will be tabulated and reviewed every 3 months.

- - 1. Data management

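### As worded, the adverse event definition ends with the study visit, so later-onset biopsy complications miss AE and SAE handling; medical events are tied to 12 months of a 24-month study

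*Protocol*

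**What the plan says.** Protocol section 8, Definition of an Adverse Event and Medical Event, limits an adverse event to "any new, undesirable medical occurrence or change of an existing condition in a subject that occurs during a study visit". Its illustration keeps to the same limit: "An adverse event could be a fall during a 6 minute walk test, a complication during a needle muscle biopsy, etc". Hospitalizations, surgery, new diagnoses and changes in symptoms are instead medical events, recorded on the Medical History Form (06), if they occur "within the 12 month period that the patient is enrolled in the study".

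Sections 8.6.e and 8.8.a both open with "A Serious Adverse Event (SAE) is defined as any adverse event that" and then list the seriousness criteria. An event must therefore be an AE before it can be an SAE.

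Other text bears on scope:
- The reporting period for AEs runs from the first protocol procedure to the last in-person visit or the end of participation.
- Participants are told to contact the coordinator about changes in health, and ongoing AEs are reviewed at visits and telephone calls.
- Section 8.6.b has staff learning of an AE "either during a study visit, phone call or through the receipt of test results".
- Section 8.6.g allows start dates to be estimated from the participant's report.
- Potential Risks, on the biopsy: "There will also be the risk of bleeding, infection, and numbness (from touching a nerve with the needle)".
- Data and Safety Monitoring states that summary data on biopsy complications and "results of post-biopsy follow up calls will be tabulated and reviewed every 3 months".

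**The concern.** Infection and delayed bleeding are named biopsy risks that can first show themselves after the participant has gone home. Under the literal definition they are not AEs, and so cannot be SAEs even if the participant is admitted to hospital. Classification decides what happens next. Severity grading belongs to the AE Log (CRF56). The SAE form (CRF57), the study PI's review (CRF59), IRB reporting and follow-up reports (CRF58) belong to SAEs. The study has no data safety monitoring board, so much of the safety oversight rests on this route. Two sites could handle the same post-biopsy infection differently, each with text to support it.

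The 12-month limit on medical events is a separate slip. The study's first purpose is to describe progression over two years, and the definition does not reach the second.

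**Working it through.** No sample-size or error-rate formula applies. The check sets the passages side by side and adds simple counts.

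**Step 1: trace one event.** Take a wound infection that begins four days after the baseline biopsy (an illustrative interval) and leads to inpatient admission.
- Did it occur during a study visit? No, so it is not an AE under the definition.
- Is it an SAE? Sections 8.6.e and 8.8.a require an AE first, so no, although it meets the hospitalization criterion.
- Is it a medical event? Yes. Hospitalization is listed there, so it goes on Form 06.
- Result: no CRF56 grade, no CRF57, no CRF59 and no IRB report through section 8.12.

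**Step 2: does the rest of section 8 share that scope?**

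| Text | Fits a visit-only definition? |
| --- | --- |
| Continuous AE reporting period | Not naturally; a visit-only scope would need only the visits |
| Learning of an AE by phone or test result (8.6.b) | Only if the event began at a visit and was noticed later |
| Estimated start date (8.6.g) | Hardly; the visit date would be known |
| SAE exemption for admissions scheduled before enrolment (8.6.e, 8.8.a) | No; it would have nothing to exempt |
| Congenital anomaly as an SAE criterion | No |
| Post-biopsy calls (Data and Safety Monitoring) | They look for what happens after the visit, but no link to CRF56 or CRF57 is stated |

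Taken together, these passages assume that AEs can begin between visits. The definition says they cannot.

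**Step 3: exposure.** From Needle biopsy procedure and Table 1:
- Planned biopsies: 60 × 2 = 120, at months 0 and 3.
- Time to the next scheduled visit: 3 − 0 = 3 months after the first biopsy and 12 − 3 = 9 months after the second.
- Table 1 does not list the post-biopsy call.

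**Step 4: the medical-event window.** The definition says 12 months. The stated purpose is two years, and visits are at 0, 12 and 24 months. The window covers 12 / 24 = 50% of participation.

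**Step 5: is year 2 still recorded?** Table 1 has medical history at month 24. Section 8 has medical events asked about at every visit and the form updated each time. The route for collecting year-2 events exists; the definition leaves them out.

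**The case against.** The strongest reply is that this is loose drafting, not a decision to exclude late events, and that the surrounding text shows the intended scope. That is largely right, and it is why the point is put as a contradiction. The definition still governs what sites enter on the log, and the SAE route depends on it.

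A reader might go further in four ways that the documents do not support.
- **That late biopsy complications are lost.** Data and Safety Monitoring requires complications and call results to be tabulated every 3 months, independently of the AE definition. Any shortfall is in the AE Log and SAE forms.
- **That all listed risks fall outside.** Numbness is attributed to the needle touching a nerve, so it arises during the procedure and is an AE. Infection and late bleeding are the clear cases. Nor is the biopsy the only invasive procedure, since blood is drawn too.
- **That the log would show 0 of 120.** This would give a one-sided 95% upper bound of 1 − 0.05^(1/120) = 2.5% (two-sided limit 1 − 0.025^(1/120) = 3.0%). It assumes that every complication is late and none is logged, and it treats two biopsies per person as independent. It is a hypothetical extreme, not an estimate.
- **That year-2 medical events go uncollected.** Step 5 shows otherwise.

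It is also fair to say that extending the definition to later events without limit would overrun the protocol's own reporting period, and that the AE Log items in 8.6.a to 8.6.i include no relatedness judgement. Both objections stand and shape the fix.

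**Conclusion.** The point holds as an internal contradiction. The literal AE definition takes biopsy complications with onset after the visit out of AE grading and SAE escalation, while the reporting period, the routes of awareness, the SAE criteria and the post-biopsy calls assume that such events count. It bears on the handling of 120 planned biopsies. How many events would be affected cannot be derived, because the protocol gives no rate of late complications; it reports no significant safety issues in the earlier paired-biopsy study of 97 patients. Separately, the 12-month phrase is wrong against a 24-month schedule and leaves half of participation outside the definition, though not necessarily outside the data. No efficacy or natural-history endpoint is affected.

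This rests on the wording of the definitions quoted. Section 8.9 and the study manual were not available. They may add reporting instructions, but the definitions would still need to be reconciled with the rest of the section.

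**What to change.** 1. Keep the present AE definition for events at a visit. Add events that begin after a visit, within the existing AE reporting period, and are possibly related to a study procedure, however they come to light, including at a post-biopsy call. The reporting period is an adequate limit: for a participant who completes the study it runs 24 − 3 = 21 months past the second biopsy.
2. Let the SAE definition in 8.6.e and 8.8.a follow from this, and say that later events unrelated to a study procedure stay on the Medical History Form.
3. Add a relatedness item to the AE Log (CRF56). At present relatedness is mentioned only for SAE review (8.13).
4. List the already planned post-biopsy call in Table 1, and state that complications reported there are entered on CRF56 and, where serious, CRF57.
5. Replace the 12-month phrase with the full period of participation, to the 24-month visit.

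The cost is one added log field, wording changes and site training. The calls and the month-24 history are already planned, so no new participant contact is needed.
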